## 1936 **Section 7 Open Ended Response and Interviewer Comments/Observations Section**

### 1937 **第七部分 开放式回答及访问者建议或观察**

1938 *Instructions to the interviewer: Say to the respondent: "Thank you for the patient responses to*  
 1939 *this exhaustive set of questions. Could you please summarize, or tell us in your own words, any*  
 1940 *additional information about the illness and/or death of your loved one?"*

1941 访问者指南：告诉回答者“谢谢你对这么多的问题进行回答付出的耐心。你能总结一下或  
 1942 者用你自己的语言告诉我们，关于你挚爱的去世的家人的一些关于疾病其他的信息吗？”

1943 *To the interviewer: Listen to what the respondent tells you in his/her own words. Do not prompt*  
 1944 *except for asking whether there was anything else after the respondent finishes. If the*  
 1945 *respondent mentions any of the following words, mark "mentioned". Tell the respondent to*  
 1946 *stop and start again if they mention a word of interest, so you have time to mark it down.*

1947 针对访问者：仔细聆听回答者告知你的关于她/他的情况。不要诱导除了询问对方是否已  
 1948 经说完。如果受访者提及以下词语，请标记“提到”。当出现关键词语时可要求受访者暂  
 1949 停叙述以便你有时间将该词语记录下来。

1950

### 1951 **Adult Checklist 成人清查清单**

|                     | Key words 关键词        | Mentioned 提及      |
|---------------------|-----------------------------|--------------------------|
| adult_7_1
成人_7_1 | Chronic Kidney Disease 慢性肾病 |  |
|                     | Dialysis 透析                 |  |

|  |                                            |   |
|--|--------------------------------------------|---|
|  | Fever 发烧                                   | ? |
|  | Heart Attack (AMI) 心脏病发作（急性心肌梗死）           | ? |
|  | Heart Problems 心脏问题                        | ? |
|  | Jaundice (yellow skin or eyes) 黄疸（皮肤或眼部发黄） | ? |
|  | Liver Failure 肝功能衰竭                        | ? |
|  | Malaria 疟疾                                 | ? |
|  | Pneumonia 肺炎                               | ? |
|  | Renal (Kidney) Failure 肾功能衰竭               | ? |
|  | Suicide 自杀                                 | ? |

1952

|                      |                                                                                               |                                                         |  |
|----------------------|-----------------------------------------------------------------------------------------------|---------------------------------------------------------|--|
| adult_7_99
成人_7_1 | Confirm that no words of interest were used during the open response.
确认在受访者叙述过程中没有出现以上关键词 | 1. No word was mentioned
没有提及词语
9. Don't know 不知道 |  |
|----------------------|-----------------------------------------------------------------------------------------------|---------------------------------------------------------|--|

1953

1954

**END OF INTERVIEW 访问结束**

1955

**THANK RESPONDENT FOR PARTICIPATION 谢谢受访者参与**

1956

1957

1958

## 9.6 Appendix A-6. Interview guide for process evaluation

### Interview guide for patients

Thank you for participating the SINEMA study in the past months. The purpose of this interview is to seek your feedback and suggestions on SINEMA intervention model that you have been involved in the past months. Your comments are appreciated and will help us improve the SINMEA intervention model to benefit more stroke patients in rural China.

The interview will last for about 30 minutes and will be recorded if consent is provided.

**Step 1:** Casually chat with the participant to establish rapport

**Step 2:** Ask the questions below:

Question 1: basic information

- When is the onset of the stroke? Any recurrence?
- What is your main problem or concern after getting the stroke?
- Who are the main person who can give you support (healthcare, mental support, etc.)?

Question 2: follow-up visit by village doctors

- How often did you visit your village doctor before the study?
- What did your village doctor do when you visit him/her (measure your blood pressure, ask questions about medication use, prescribe new medicine, etc.)?
- Compared to previous doctor visit, did you spend more time to talk to your doctor than before?
- Do you think the APP helped the village doctor? Do you have any suggestions to them?
- Is it necessary that the village doctors follow-up you monthly and last for a whole year?

Question 3: take medicines

- Which medicines are you taking? How many time do you take every day?
- Did you take medicines everyday according to the medicine prescription by your village doctors? Any trouble in taking medicines? (forgot, feel better and stop, etc.)
- Did you use the calendar to record the date that you take the medicines? Any better ways?

Question 4: Text and voice messages

- Do you share phone with your family member? Do you use the phone everyday?
- Did you receive text messages (how many, when)?
- Do you have difficulties in reading them? What information did you learn from the text messages? Did you try to follow the suggestions from the text messages to change your lifestyles (eg. stop smoking, healthy eating, adhere to medication use, doing physical activities, etc.)?
- Did you receive voice messages (how many, when)?
- Do you have difficulties in listening them? What information did you learn from the text messages? Did you try to follow the suggestions from the text messages to change your lifestyles?
- In general, which way do you prefer? Do you think these messages could help you to change your lifestyle behaviour?

Question 5: Other comments and suggestions?

**Step 3:** Thank the interviewee for their time and hand over small gift.

## **Interview guide for Village doctors, township and county managers**

Thank you for participating the SINEMA study in the past months. The purpose of this interview is to seek your feedback and suggestions on SINEMA intervention model that you have been involved in the past months and on SINEMA application that you have used in the past months. Your comments are appreciated and will help us improve the SINMEA intervention model and the SINEMA application to benefit more stroke patients in rural China.

The interview will last for about 30 minutes and will be recorded if consent is provided.

**Step 1:** Casually chat with the participant to establish rapport

**Step 2:** Ask the questions below:

Questions 1: stroke management in China

- What are the main difficulties of prevention and management of stroke in primary settings?
- Can the national basic public health service meet the needs of stroke secondary prevention?
- Compared with the current national public health service system (paper + online system), what are the advantages and disadvantages of the APP?

Question 2: Training

- Do you think your medical knowledge has been improved after the training? In what way?
- Which part of the training do you like best? Which part of the training is unnecessary and should be deleted?
- Is there any information you think is important but has not been covered in our training? Is there any information that you think is too easy for you and do not need to be trained?
- Is the training on APP use enough? Will you use the training section on the APP?
- Any other suggestions?

Question 3: Follow-up visit

- How did you follow-up the patients involved in this study in your village? In the clinics or at patients' home?
- How did you usually your work and our follow-ups? Did you follow-up them all on the same day or on different days?
- How do you think of the workload (high, medium, low)? Can you keep conducting the one-year intervention on 25 patients?
- On average, how long did you use in following up one patient? Did you find any difficulties in following up patients?
- Do you think your patients followed your suggestions on medication use? How did you evaluate their medication adherence? Did they record their medication use every day?
- How did you measure their blood pressure? How many times?

Question 4: SINEMA APP

- Is it difficult to learn to use the APP?
- Does the APP help you better manage your patients or you think the APP burdened you heavily?

2051       • Did you use your own SIM card or WIFI?  
2052       • Any suggestions on improving the design of the APP?  
2053  
2054   Question 5: Key performance indicators, compensations and management  
2055       • Any better key performance indicators?  
2056       • Do you think the salary we give to you is equivalent to your expectation?  
2057       • How do you evaluate the manger in township hospital? Do you think they provide enough  
2058       support for you?  
2059       • Do you this the Wechat group is useful?  
2060  
2061   Question 6: Other comments and suggestions?  
2062  
2063   **Step 3:** Thank the interviewee for their time and hand over small gift.  
2064  
2065

2066

2067

2068

2069

2070

2071

2072

2073

2074

2075

2076

2077

2078

# **Part B: Protocol for the long-term observational follow-up of the SINEMA trial**

**Version Date: August 10th, 2022**

## 1. AIMS

To investigate the long-term effectiveness of the one-year SINEMA intervention on major outcomes:

- To conduct follow-up assessment of surviving participants and investigate the long-term effects of the SINEMA intervention on primary outcomes (blood pressure) and secondary outcomes (medication use and adherence, stroke recurrence, hospitalization, disability, and mortality).
- To collect detailed information about vital status of deceased participants and analyze the effect of the SINEMA intervention on mortality.

## 2. ETHICS REVIEW AND HUMAN SUBJECT PROTECTION

### 2.1 Ethical review

The study was approved by the ethical boards of Chinese Academy of Medical Sciences & Peking Union Medical College (CAMS & PUMC-IEC-2022-062) and the Duke University (Pro00082130-AMD-9.1). All participants will provide written informed consent.

### 2.2 Participant informed consent

All participants will provide written informed consent.

#### *Written informed consent from stroke patients participating the study*

A written informed consent will be obtained from patients (**Appendix B-1**). Before the recruitment, village doctors will introduce the study to all prospective participants and invite them to participate in the study. On the day of recruitment, the trained research staffs will present the information to all prospective participants. Then, a one-on-one meeting will be organized between prospective participants and research staffs in a private space. Research staffs will address questions and concerns that prospective participants have and then ask their decision. The overall consent discussion will take about 10-15 minutes. Patients will have a copy of the form with contact information.

#### *Written informed consent for village doctors participating the study*

A written informed consent will be obtained from village doctors (VDs) before the interview (**Appendix B-1**). The trained research staffs will conduct the consent process at a private place. The research staffs will present the information on the consent document and answer questions from the interviewees. The overall consent discussion may take about 10-15 minutes. Interviewees will have a copy of the informed consent form with the contact information.

#### *Written informed consent from the family member for participating the verbal autopsy interview*

A written informed consent will be also obtained from the family member before the verbal autopsy interview (**Appendix B-1**). The trained research staffs will contact the interviewees in advance and conduct the consent process at a private place. The overall consent discussion may take about 20-30 minutes. Interviewees will have a copy of the informed consent form with the contact information.

2119

## 2120 **3. STUDY DESIGN**

### 2121 **3.1 Study design, setting, and participants**

2122 This study is a 4.5-year post-trial follow-up of the SINEMA trial, a community-based, open-label,  
2123 two arm, cluster-randomized controlled trial conducted in fifty villages in rural Hebei, China. The  
2124 detailed trial design has been described previously. Briefly, eligible participants were  
2125 community-dwelling adults living in the recruited villages with a history of stroke diagnosed at  
2126 the county- or higher-level hospitals and in a clinically stable condition with at least basic  
2127 communication abilities. Individuals were excluded if they were bedridden, had severe life-  
2128 threatening diseases with an expected life span shorter than 6 months, and declined consent.  
2129 Recruitment took place between June and July 2017.

2130 Randomization, performed by a biostatistician unaware of the clusters by using a computer-  
2131 generated random numbering system, allocated the fifty villages in a 1:1 ratio with stratification  
2132 by township to either the SINEMA intervention or control arm. A follow-up assessment was  
2133 conducted by blinded assessors in July 2018, where 1266 surviving participants completed the  
2134 assessment.

2135 The active phase of the intervention spanned from July 2017 to July 2018, post which the  
2136 intervention concluded, though village doctors could optionally continue offering these services  
2137 without financial incentive or further project support.

2138

### 2139 **3.2 Procedures of follow-up assessment among participants**

2140 All surviving participants, regardless of their follow-up status at 12 months, of the SINEMA trial  
2141 will be invited to participate in a 5-year follow-up.

2142 Information on the vital status of the participants will be provided by village doctors, which  
2143 enabled the generation of a list of survival participants who are eligible to participate in the  
2144 survey and a list of deceased participants whose vital status, date and cause of deaths will be  
2145 further collected.

#### 2146 **3.2.1 Follow-up assessment for survived participants**

2147 For all survived participants, they will be contacted by corresponding VDs to inform them about  
2148 the study. They will be invited to come to the corresponding village clinics to complete the post-  
2149 trial assessment. The post-trial assessment for survivors will be performed by blinded outcome  
2150 assessors, who are staff members from Centers for Disease Control (CDC) in a nearby county  
2151 and received training for assessment. These assessors will follow the standard protocol to  
2152 measure outcomes uniformly across all villages and participants, consistent with previous  
2153 assessment at baseline and 12 months. The assessment consists of surveys will be  
2154 administered through face-to-face interviews (**Appendix B-2**) with responses will be recorded in  
2155 an online survey platform (Qualtrics, Provo, UT), and standard anthropometric measures.

2156

### 3.2.2 Data collection for deceased participants

For deceased participants, we will employ a multifaceted approach to collect information on the date and cause of death from three major sources to gain the most reliable information. Firstly, we will utilize participants' unique ID numbers to link them to the local Center for Disease Control and integrate this data with the local death registration system. Secondly, to account for potential delays in the death records' updates, we will also independently collect vital status information through a standardized Excel form, including death dates and causes, from village doctors for all 50 villages. This information will supplement the CDC data. Thirdly, when there is key information missing or major inconsistency between two available sources, we will conduct a smartphone-based shortened version of verbal autopsy (VA) survey to informative family members of some selected dead participants by using Population Health Metrics Consortium (PHMRC) Shortened Questionnaire adult module. Trained health workers will conduct the VA interview. The procedure for the verbal autopsy survey will remain consistent with the one-year follow-up, with trained data collector administering a shortened version of the survey via smartphone to family members of deceased participants.

### 3.2.3 Strategies to improve follow-up rate

To improve the follow-up rate, the following strategies will be performed: Participants whose village doctors informed that they have moved outside of the village, the last known residence will be contacted to provide the address and contact information of the participants if possible.

- (1) For participants who have relocated to other villages within the Nanhe county and in villages where the survey is planned, participants will be invited to participate in the survey of the corresponding villages.
- (2) For participants who have relocated within the county but in the area that were not involved in the SINEMA study, a team of researcher will contact them and schedule a door-to-door survey for follow-up assessment.
- (3) For participants who have relocated outside of the county, the research team and the data collection team will discuss the feasibility of performing data collection outside of the county.
- (4) Participants will be considered as lost to follow-up when known alive, but the participants were not able to complete the assessment following the previous mentioned procedure or refuse to participate in the study.

For patients with mental health issues or other severe diseases that may present difficulties for them to complete the survey, the data collection will be conducted with accompany of family member if possible. Family members may provide proxy responses to certain questions and the data collectors will label proxy responses where appropriate.

## 3.3 Outcomes evaluation and measurement

The outcomes for follow-up assessment will be in the same way of the baseline and 12-month follow-up assessment. Table B-1 illustrate all the key aspects of measurement by comparing with baseline and 12-month follow-up assessment.

### 3.3.1 Primary outcomes

#### *Systolic blood pressure*

Systolic BP, the primary outcome of the SINEMA trial, is also the primary outcome of interests for this post-trial follow-up assessment. Systolic BP, will be analyzed as the differences between arms in the change of BP from baseline to 4-year post-trial. In line with previous assessments, BP will be measured on the right upper arm while the participants are seated, following 5 minutes of quiet rest, using an electronic BP monitor (Omron HEM7052). Two measurements will be obtained, with the mean value calculated. If the difference between the first two systolic BP readings exceeds 10 mmHg, a third measurement will be taken and the last two readings will be used for calculation.

#### *Mortality*

Mortality, an exploratory outcome of the original trial, will be considered as a key primary outcome of interests for the follow-up assessment considering the relatively long follow-up period. Date and cause of deaths will be collected from multiple approaches as mentioned above.

### 3.3.2 Secondary outcomes

The secondary outcomes of interests will be in line with the original protocol, including diastolic blood pressure, medication adherence (measured by using 4-item Morisky Green Levine Scale), physical activity level (measured by using IPAQ-short form), mobility (measured by using Timed-up and go test), health-related quality of life (measured by using EQ-5D-5L), disability (measured by using modified Rankin Scale), stroke recurrence (measured by self-reported experience of stroke recurrence) and stroke-related hospitalization (measured by self-reported history of hospitalization).

### 3.3.3 Additional measurement in follow-up assessment

The follow-up assessment will add a few measurements that were not included in the original trial, but could be important for assessing the health status of individuals living with stroke.

#### *(1) Cognitive function*

It has been confirmed that stroke could result in the cognitive impairment. Many stroke patients suffer cognitive decline after stroke. We will measure the cognitive function by using The Community Screening Instrument for Dementia (CSI-D). The Chinese version of CSI-D has been validated to be a reliable and educationally independent screening instrument for dementia sensitive to detect early stage of the disease.

#### *(2) Functional dependence*

Many stroke patients suffer functional dependence post stroke. Functional independence is a key factor in stroke rehabilitation. We will measure the functional dependence using activities of daily living (ADL) and instrumental activities of daily living (IADL) scales. ADL and IADL are considered a primary functional status measure in stroke rehabilitation because of their relative objectivity, simplicity, and relevance to patients.

2236 (3) Grip strength test

2237 We also performed grip strength tests for both hands among participants. The measurement was taken  
 2238 by using grip strength tools (Yuejian™ WL-1000, Nantong, China), which has been used in other studies  
 2239 previously as a standardized tool for grip strength assessment.

2240 **Table B-1. Schedule of assessments of SINEMA post-trial study**

| Aspect of data collection                                      | Baseline | 1-year follow-up | Post-trial follow-up |
|----------------------------------------------------------------|----------|------------------|----------------------|
| Questionnaire                                           |          |                  |                      |
| Demographics                                                   | √        | √                | √                    |
| Family information                                             | √        | √                | √                    |
| Lifestyle risk factors                                         | √        | √                | √                    |
| Disease history                                                | √        | √                | √                    |
| Cognitive function (CSI-D)                                     |          |                  | √                    |
| Disability (modified Rankin scale)                             | √        | √                | √                    |
| Functional dependence (ADL)                                    |          |                  | √                    |
| Health-related Quality of life (EQ-5D-5L)                      | √        | √                | √                    |
| Depression (PHQ-2 and PHQ-9)                                   | √        | √                | √                    |
| Medication adherence (4 item4-item Morisky Green Levine Scale) | √        | √                | √                    |
| Physical measurement                                    |          |                  |                      |
| Time up and go                                                 | √        | √                | √                    |
| Height                                                         | √        | √                | √                    |
| Weight                                                         | √        | √                | √                    |
| Waist circumference                                            | √        | √                | √                    |
| Neck circumference                                             |          |                  | √                    |
| Grip strength                                                  |          |                  | √                    |
| Blood pressure                                                 | √        | √                | √                    |

2241

2242 **3.4 Statistical analysis**

2243 **3.4.1 General analysis**

2244 The analysis for major outcomes will be in the same way in line with the 12-month follow-up  
 2245 assessment, according to the published statistical analysis plan. The intention-to-treat principle  
 2246 will be used for all analyses. Descriptive analysis will be performed with means and standard  
 2247 deviations (SDs) or medians and quartiles for continuous variables, and counts and  
 2248 percentages for binary variables. The analysis of all continuous or binary outcomes, apart from  
 2249 mortality, remains consistent with the one-year follow-up statistical analysis plan. Specifically,  
 2250 for continuous variables, we will use mixed-effects linear regression to estimate differences  
 2251 between two arms in the outcomes from baseline to 12 months and 5.5-year post-baseline, with  
 2252 random intercept for village (cluster) and fixed effect for township. The main model will adjust for  
 2253 age, sex, and baseline outcome, and removed outliers based on an a priori decision to exclude  
 2254 values more than two interquartile ranges above the third quartile or below the first quartile of  
 2255 the distribution. In instances where the mixed effects model did not converge, we will employ  
 2256 the generalized estimating equations method by fitting a Gaussian model with an identity link.

For binary outcomes, generalized estimating equations approach will be adopted to obtain population-average treatment effect and similar adjustment on township, age, sex, and baseline outcome was made. We will use a Poisson model with log link and robust standard errors to obtain risk ratios and with identity link to obtain risk differences. If models did not converge, we will use a marginal standardization approach by fitting a binomial model with a logit link to obtain risk differences and risk ratios.

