## 7. STATISTICAL ANALYSIS PLAN

### 7.1 General analysis principles

#### 7.1.1 Participant population.

Patient-level outcome data will be used, and stratification and clustering will be taken into account in all analyses. The analysis population will consist of all enrolled participants who completed the baseline assessment. Missing follow-up measurements due to (1) death, (2) moving away from the study area, or (3) refusing to participate in the follow-up assessment will be accounted for in the analyses.

The analysis will use the intention-to-treat principle whereby all participant-level outcome data will be analyzed according to the arm to which the patient was allocated. Given the challenges of defining protocol violation in the context of a complex multi-component intervention like SINEMA, we will not perform per-protocol analyses but will instead summarize adherence to intervention components among intervention-arm participants and will summarize the frequency of visits to the village clinic in the control arm.

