#### 7.1.2 Presentation and data handling rules.

Continuous variables will be reported as mean and standard deviation, if symmetric, or as median with 25th and 75th percentile, if not. Counts and proportions will be reported for categorical variables. Outliers will be identified through boxplots and histograms and will be queried at the data checking stage if an error is suspected. Ninety-five percent confidence

intervals will be presented, and significance of the primary outcome will be assessed based on a test at the two-sided 5% significance level.

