| Mobility             | 
DBP.
 
Mobility is measured using the “Timed Up and Go” test, a functional mobility test that requires the participants to stand up, walk 3 meters, turn, walk back and sit down. The mobility outcome will be specifically measured by the total time taken to complete the test, for which faster times (i.e. lower values) represent better functional mobility status. For participants who cannot complete the test (e.g. who cannot stand up), we will use a range of strategies (i.e. set to missing, set at maximum observed time or at some larger maximal tie) to deal with this issue and will evaluate how sensitive the estimated intervention effect is to those assumptions. The variable will also be dichotomized at a cut-off of 14s based on previous studies.
 | Continuous as total time to complete the test; and binary using cutoff of 14s                          |
| Physical activity    | 
Physical activity is measured with the short version of the International Physical Activity Questionnaire. Total physical activity score (MET-minutes/week) and activity classification (inactive, minimally active and health enhancing physical activity-HEPA) are derived according to the IPAQ scoring guideline.
                                                                                                                                                                                                                                                                                                                                                                                                                                                                  | Continuous as total physical activity score; and binary using cutoff of HEPA active vs. HEPA inactive. |

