#### 3.4.4 Sensitivity analyses

Following the previous statistical analysis plan, sensitivity analyses will be performed involved additional adjustment for covariates that were statistically imbalanced between arms at baseline, associated with the status of loss to follow-up, or both, as well as include all outliers.

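### Part B's main model for continuous outcomes drops values beyond two interquartile ranges without requiring a suspected error; the all-values analysis should be the main one and the exclusion the sensitivity analysis

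*Combined protocol and SAP*

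**What the plan says.** Part B 3.4.1 describes the main mixed-effects model for continuous outcomes. It adjusts for age, sex and baseline outcome, and it "removed outliers based on an a priori decision to exclude" "values more than two interquartile ranges above the third quartile or below the first quartile of" the distribution. The rule is credited to reference 71, a separately published statistical analysis plan. No suspicion of error is required.

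The same section says that "The intention-to-treat principle" governs all analyses. It also says that the analysis of every continuous or binary outcome other than mortality "remains consistent with the one-year follow-up statistical analysis plan".

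The one-year plan supplied in Part A reads differently:

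- 7.1.1 states intention-to-treat as the principle "whereby all participant-level outcome data will be analyzed according to the arm to which the patient was allocated".
- 7.1.2 says: "Outliers will be identified through boxplots and histograms and will be queried at the data checking stage if an error is suspected". It contains no exclusion rule.
- 7.3.1 expects mobility, physical activity and quality of life to be right-skewed. If model assumptions fail it turns to bootstrapping, a log transformation or, for Timed Up and Go, a time-to-event analysis.
- Table 4 lists several options for people who cannot complete Timed Up and Go: "set to missing, set at maximum observed time or at some larger maximal tie".

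Part B 3.4.4 then plans sensitivity analyses with extra covariate adjustment "as well as include all outliers".

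**The concern.** The main model selects participants by the value of the outcome, which is measured after randomisation. Randomisation does not protect such a selection. If the intervention shifts a skewed outcome, the arm with the longer upper tail loses more people, and the difference in means is computed on what remains.

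The direction depends on the scale. For Timed Up and Go a long time is bad, so the upper cut-off removes the worst results. For MET-minutes a high value is good, so it removes the best. In both cases the raw difference shrinks. Non-completers of Timed Up and Go are a special case: if they are set at a maximum or larger time that lies beyond the cut-off, the rule takes out the people whom that option was meant to keep.

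At stake are the reported effect sizes for secondary continuous outcomes, and a main analysis that does not match its own stated principle.

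**Working it through.** **1. Plan's own figures.** The documents attach no number to the outlier rule. The one design figure, 83% power in Part A 5.3, reproduces: design effect 1 + (24 − 1) × 0.04 = 1.92; effective n per arm 23 × 24 / 1.92 = 287.5; noncentral t on 2 × 23 − 2 = 44 df gives 83.4%. It does not bear on the rule.

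**2. Near-normal outcome (systolic pressure).** The quartiles lie at ±0.6745 SD, so the IQR is 1.349 SD. The cut-off is 0.6745 + 2 × 1.349 = 3.372 SD. Share removed: 2 × (1 − Φ(3.372)) = 0.00075, or about 0.07%. On the 1266 participants assessed at 12 months (used only for scale) that is about 1 person. Heavier tails remove more: 0.6% for a t distribution with 10 df and 2.1% with 4 df.

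**3. Right-skewed outcome.** The documents give no distribution, so I assume a log-normal with log SD s. Relative to the median, the upper cut-off is U = e^(0.6745s) + 2 × (e^(0.6745s) − e^(−0.6745s)), and the share removed is 1 − Φ(ln U / s). For s = 0.5: U = 1.401 + 2 × (1.401 − 0.714) = 2.776; ln U / s = 2.042; share 2.1%. The lower cut-off is 0.714 − 2 × 0.687 = −0.66, below zero, so nothing is removed at the bottom.

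**4. Effect on the comparison.** Simulation with millions of values per arm, a true intervention-to-control ratio of 0.9, and the cut-off computed on pooled data:

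| Log SD | Removed, single log-normal | Of 1266 | Removed, control / intervention | Raw difference retained | Standardised difference retained |
|---|---|---|---|---|---|
| 0.5 | 2.1% | 26 | 2.6% / 1.6% | 0.81 | 0.97 |
| 0.6 | 2.8% | 35 | 3.3% / 2.2% | 0.75 | 0.97 |
| 0.8 | 4.2% | 53 | 4.8% / 3.6% | 0.62 | 1.00 |
| 1.0 | 5.7% | 72 | 6.3% / 5.1% | 0.50 | 1.04 |

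Simulation error in the last two columns is about 0.01. In seconds, with an assumed control median of 14 s and s = 0.5, a Timed Up and Go difference of −1.58 s becomes −1.28 s (1.28 / 1.58 = 0.81).

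A true 10% increase, the favourable direction for MET-minutes, gives almost the same retained shares (0.81 to 0.50). The imbalance then reverses: at s = 0.6, 2.3% of control and 3.3% of intervention values are removed.

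The standardised difference holds up because the exclusion also lowers the SD.

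**5. Benefit confined to the tail (stress case, all inputs assumed).** Suppose most times are near 14 s, and 10% of controls but 5% of intervention participants are near 60 s. The cut-off falls at about 31 s, and the rule removes 10.3% and 5.3%. The difference goes from −2.3 s to about 0.

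**6. Non-completers.** With a log-normal at s = 0.4 or 0.5 and n = 1266, the sample maximum exceeded the cut-off in all 2,000 simulated samples. Under those assumptions, anyone set at the maximum observed time would be excluded.

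**The case against.** The case for leaving the rule alone has several sound parts.

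- **The full result will exist.** Part B 3.4.4 already plans an analysis that keeps every outlier. The dispute is over which of two stated analyses is the main one.
- **Primary outcomes are hardly touched.** A reader might infer that the long-term conclusion on systolic pressure is at risk. The documents do not support that: a near-normal outcome loses about 0.07%, and mortality is analysed with Cox models that the rule does not enter. The rule is written for continuous outcomes, so the binary versions in Table 4 (14 s cut-off, HEPA status) are also unaffected.
- **The test is not much weaker.** In the log-normal case the standardised difference stays within a few percent, and the raw bias is toward the null. This stands for a proportional effect. It fails if the benefit sits in the severe tail (working, item 5), but nothing in the documents shows that it does.
- **The rule may be prespecified.** Reference 71 is not among these documents, so a charge that the rule was chosen after seeing data cannot be supported. Prespecification would not make an outcome-dependent exclusion unbiased, and it would not reconcile 3.4.1 with the plan supplied here.
- **Analysis by allocated arm is preserved.** The conflict is only with the requirement that all outcome data be used.

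Two other strong readings fail. The rule does not remove the worst results of every skewed outcome: for MET-minutes it removes the best, as it would for quality of life if that is right-skewed as 7.3.1 expects. Nor does it necessarily delete Timed Up and Go non-completers: Table 4 offers several options, one of which sets them to missing, and only an assigned time beyond the cut-off would be excluded.

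The size of the effect also depends on something 3.4.1 leaves open: whether the distribution is of the value or the change, pooled or by arm, and at which visit.

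**Conclusion.** The point holds as an internal conflict and an avoidable bias in secondary continuous outcomes. Part B 3.4.1 cannot both apply intention-to-treat, as Part A 7.1.1 words it, and drop outcome values from the main model without suspicion of error. Part A 7.1.2 and 7.3.1 supply no such rule and already provide other tools for skew.

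The retained raw difference is about 81% to 50% for log SD 0.5 to 1.0, with unequal exclusion by arm. That range rests on a log-normal outcome, a 10% proportional effect and a pooled cut-off on the raw value; none of these comes from the documents. The expected loss for systolic pressure is about 0.07% if it is near normal. Severity is should-fix: the outcomes affected are secondary, and the all-values result is already planned.

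**What to change.** Swap the roles of the two analyses in Part B. In 3.4.1, fit the main model to all observed values and correct only confirmed data errors after query, in line with Part A 7.1.2. In 3.4.4, make the two-IQR exclusion the sensitivity analysis. For skewed outcomes, carry over the bootstrap or log-transformation options from Part A 7.3.1.

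For the exclusion analysis, state whether the cut-off is computed on the outcome or its change, pooled or by arm, and at which visit. State how it applies to Timed Up and Go non-completers who are given an assigned time. Report the number excluded by arm and outcome.

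If the sponsor keeps the present order, 3.4.1 still has to be reconciled with Part A 7.1.1, 7.1.2 and Table 4, and should no longer claim intention-to-treat without qualification.

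The cost is SAP wording. Both analyses are already planned, and no new data or change in sample size is needed.
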